##### Decision coaching

The coaching takes place in person or, if necessary, by telephone or online. The coaching process follows the sections of the HELP decision aid: patient’s information needs, the preferred method of decision-making, and the clarification of central personal values.

After the coaching session and before the consultation with the physician, participants fill in the questionnaires (Decisional Conflict Scale, Decision Self-Efficacy Scale, Preparation for Decision Making Scale, EQ 5D, Hospital Anxiety and Depression Scale) before their consultation with the physician. After the consultation, the post-survey questionnaires are handed out or mailed to participants (Patient Involvement in Care Scale, EQ-5D, Hospital Anxiety and Depression Scale).

#### Control group

The participants in the control group get usual care, i.e., the doctor-patient conversation takes place without preliminary coaching and deliberation about their preferences and goals.

Before the consultation with their physician, participants fill in the pre-survey questionnaires (Decisional Conflict Scale, Decision Self-Efficacy Scale, EQ 5D, Hospital Anxiety and Depression Scale). After the consultation, the post-survey questionnaires are handed out or mailed to them (Patient Involvement in Care Scale, EQ-5D, Hospital Anxiety and Depression Scale).

### Criteria for discontinuing or modifying allocated interventions {11b}

Patients can leave the study at any time for any reason, without any consequences. If a patient’s health status declines and they are no longer able to answer the survey questions, they will be treated as a dropout. The same applies for participants who withdraw their consent for any other reason. Patient data collected up to that moment will not be included in the analysis.

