### Methods in analysis to handle protocol non-adherence and any statistical methods to handle missing data {20c}

#### Analysis population

As analysis populations, the two common populations of intention-to-treat and per-protocol are defined and used. The intention-to-treat population considers all patients as randomized regardless of whether they finished the whole survey procedure. Criteria for determining the per-protocol population are as follows: patients who stayed in their randomized group, answered the first questionnaire before the decision-making (and for IG: after the intervention), and answered the second questionnaire within the timeframe of 1–4 weeks after the treatment decision.

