#### Missing data

Missing data might occur by patients’ withdrawal from trial, unreturned questionnaires after the consultation, or other circumstances. Reasons for withdrawal will be reported for each randomization group and compared qualitatively. The effect that any missing data might have on results will be assessed via sensitivity analysis of augmented data sets. Dropouts and item nonresponse will be included in the analysis by imputation methods for missing data. Missing values in the primary outcome (and in other outcomes) are replaced by multiple imputation. Through an iterative series of predictive models using the non-missing variables in the dataset, the imputation is conducted. The iterations are run until it appears that convergence has been met. The accuracy of the imputations will depend on the information density in the dataset. Diagnostic plots are used to determine how valid the imputations may be. Imputation is conducted via predictive mean matching (PMM). PMM involves selecting a datapoint from the original, non-missing data which has a predicted value close to the predicted value of the missing sample. The closest values are chosen as candidates, from which a value is chosen at random. After the imputations are completed, all of the data (complete and imputed) will be combined and the analysis performed for each imputed and completed dataset.

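### The dropout rule in 11b removes data that the intention-to-treat and imputation rules in 20c keep, including primary scores already observed

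*Protocol article*

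**What the plan says.** Section 11b (criteria for discontinuing or modifying allocated interventions) names two kinds of dropout. The first is clinical: "If a patient’s health status declines and they are no longer able to answer the survey questions, they will be treated as a dropout". The second is withdrawal: "The same applies for participants who withdraw their consent for any other reason". The paragraph then closes, without separating the two: "Patient data collected up to that moment will not be included in the analysis".

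Section 20c gives different rules. Under Analysis population: "The intention-to-treat population considers all patients as randomized regardless of whether they finished the whole survey procedure". Under Missing data, withdrawal is listed as one source of missing values ("Missing data might occur by patients’ withdrawal from trial, unreturned questionnaires after the consultation, or other circumstances"), and the remedy is stated twice: "Dropouts and item nonresponse will be included in the analysis by imputation methods for missing data" and "Missing values in the primary outcome (and in other outcomes) are replaced by multiple imputation". Table 2 lists the per-protocol analysis under sensitivity analyses, so intention-to-treat is the implied primary population.

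The primary outcome is the values-clarity subscore of the DCS. For the intervention group, the Decision coaching section says: "After the coaching session and before the consultation with the physician, participants fill in the questionnaires". The Control group section also places the DCS before the consultation. A second set of questionnaires follows the consultation, and the Participant timeline section puts 1–4 weeks between the two.

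**The concern.** One section takes dropouts' data out of the analysis and the other keeps dropouts in it. Both cannot be followed, and the article does not rank them. Because the primary score is obtained at the first questionnaire, a patient can have a complete primary outcome and still become a dropout before the second. Patients in this trial have stage IIIb, IIIc or IV lung cancer, so decline within that interval is a realistic event.

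Two things are at stake. First, decline in health may be related to the outcome, and dropout may differ by arm because only one arm is asked to attend coaching and the trial is open. Leaving such patients out can bias the contrast. Second, the choice between the rules is left to whoever performs the analysis of an unblinded trial.

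**Working it through.** **Step 1: the rules side by side.** Take a patient who returned the pre-consultation DCS and then became too ill for the second questionnaire.

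| Rule followed | Observed primary score | Patient in the primary analysis? |
|---|---|---|
| 11b alone | removed | no |
| 20c alone | used as observed | yes; only later outcomes are imputed |
| 11b, then 20c | removed | yes, with an imputed value in place of the real one |

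In the third row, the patient's other answers from the same questionnaire are removed too. The imputation model then has little beyond arm and stratum to predict from.

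**Step 2: reproduce the plan's sample size.** Inputs from the Sample size section: difference 10, SD 20.6, two-sided 5%, power 80%, Mann-Whitney test, 20% dropout.

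- Normal approximation: n = 2 × (1.96 + 0.84)² × 20.6² / 10², rounded up to 67 per group.
- Mann-Whitney efficiency 3/π: 67 / 0.955 = 70.2, rounded up to 71.
- Simulation with normal data (40,000 runs): power 0.803 at 71 per group.
- Inflation: 71 / (1 − 0.20) = 88.75, rounded up to 89 per group, 178 in total.

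The stated figures hold. If 11b removed every planned dropout, about 71 per group would remain, with power about 0.80 as planned. If every primary score were observed and kept (89 per group, an upper bound), simulated power would be 0.88. That is an unused gain, not a shortfall.

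**Step 3: how many patients.** 0.20 × 178 = 35.6, about 36. This is a ceiling: the 20% is not split by reason, and some dropouts will never have given a score. The share who have is not in the article. If it is half, about 18 observed scores are at risk (0.5 × 35.6 = 17.8); at 25% to 75%, about 9 to 27.

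**Step 4: size of the avoidable shift (illustration).** Assumptions, none of them in the article: dropout 25% in the intervention arm and 15% in the control arm; a share s of dropouts has an observed score; dropouts score d points worse than the others in their arm, with d = 10 to 15.

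Only dropouts with a score can be lost to, or recovered from, the 11b rule. In an arm with dropout D, they form the fraction sD / (1 − D(1 − s)) of all observed scores. Excluding them shifts the contrast by d times the difference of this fraction between arms.

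- s = 0.5: 0.125/0.875 − 0.075/0.925 = 0.143 − 0.081 = 0.062; shift 0.6 to 0.9 points.
- s = 0.25: 0.0625/0.8125 − 0.0375/0.8875 = 0.035; shift 0.3 to 0.5 points.
- s = 0.75: 0.1875/0.9375 − 0.1125/0.9625 = 0.083; shift 0.8 to 1.2 points.

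With equal dropout in the two arms and the same d and s, the difference of fractions is zero and there is no shift. With more dropout in the intervention arm, the shift favours the intervention.

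**The case against.** The strongest reply is that section 20c is the dedicated place for analysis populations and missing data, while 11b is a paragraph on discontinuation. A careful analyst would follow 20c, and then nothing is lost. A reader might infer from 11b that the primary analysis is a completers analysis. The document does not support that as a fact: it follows only if 11b overrides 20c. Nor does 11b clearly cover everyone who stops. Section 20c lists unreturned questionnaires separately from withdrawal, so a patient who simply does not send back the second questionnaire need not fall under 11b. This part of the objection stands and makes the consequence conditional.

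A reader might also infer that the trial is underpowered. It is not: the inflation from 71 to 89 already allows for losing 20%.

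One might size the bias as (0.25 − 0.15) × 10 to 15 = 1.0 to 1.5 points. That supposes that every dropout had an observed score. Patients who never gave one are missing under either rule, so this part cannot be charged to 11b.

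Finally, removal may be proper for patients who withdraw consent. The consent form is not at hand, and the article refers to German data-protection law. This stands for the withdrawal group, and the fix must allow for it. It does not explain the same removal for patients who are only too ill to continue, whom the sentence in 11b also covers.

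What the objection leaves untouched is that the two sections conflict and the article gives no order of precedence.

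**Conclusion.** The contradiction is real and must be resolved, because it decides who is in the primary analysis. If 11b governs, the primary analysis moves towards a completers set, close to the per-protocol set that is meant to serve as its sensitivity analysis. If 11b and 20c are both applied, an observed value gives way to an imputed one.

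The harm is loss of the intention-to-treat population and possible selection bias; the stated 80% power is preserved. At most about 36 of 178 patients are affected. The avoidable shift is about 0.6 to 0.9 points, or 6% to 9% of the 10-point target, if dropout is 25% against 15%, half of dropouts have a score, and they are 10 to 15 points worse. These are illustrative assumptions; equal dropout under the same assumptions would give no shift. The case is clearest for patients lost through declining health.

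**What to change.** Replace the last sentence of 11b with text to this effect: data collected up to dropout are retained and analysed in the randomised group; decline in health counts as loss to follow-up; data are removed only where the participant asks for deletion or the consent terms require it, and such removals are counted and reported by arm.

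Add to 20c that the primary analysis uses every observed pre-consultation DCS score, and that imputation applies only to scores never obtained or required to be deleted.

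The cost is a short amendment, which the article's section on protocol amendments makes subject to agreement of the research team and ethics approval. It needs no further patients or data. Recruitment was due to end about 31.01.2023, before the article appeared, so the wording for withdrawn patients must be checked against the consent that participants signed. The change is most useful if made before the outcome data are analysed.

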### Strategies to improve adherence to interventions {11c}

The adherence to fill out the questionnaires before and after the conversation with the physician takes place is ensured by friendly reminders via phone call or mail. Intervention adherence, i.e., ensuring that patients show up for the arranged coaching session, is ensured by reminding patients via phone call one day ahead of the appointment.

### Relevant concomitant care permitted or prohibited during the trial {11d}

As the intervention does not consist of any form of medical treatment, there are no restrictions concerning medical treatments.

### Provisions for post-trial care {30}

No provisions for ancillary and post-trial care will be provided, due to the absence of any physical intervention and the shortness of study.

### Outcomes {12}

The main objective is to investigate the effectiveness of the developed decision support and decision coaching for lung cancer patients. Effects will be measured by the sum score of the dimension “clarity of personal attitude” (items 4-6) of the Decisional Conflict Scale (DCS) [16, 17] after the decision coaching.

In addition, the effects of the HELP intervention on patients’ self-efficacy, their perceived preparation for and participation in treatment decision-making, and the patients’ emotional state will be assessed.

#### Primary outcome

The primary outcome is the sum score of the dimension “clarity of personal attitude” in the Decisional Conflict Scale (DCS) after the decision coaching has taken place. The questionnaire is validated in German and shows good reliability [16, 17].

A clinically relevant difference of 10 points in the primary outcome between the two treatment groups was assumed to be appropriate for case planning.

#### Secondary outcomes

Secondary outcomes are the effects of the HELP intervention on patients’ self-efficacy, their perceived preparation for and involvement in treatment decision-making, and their emotional state. All questionnaires listed in Table 1 are validated and show good reliability (see item 18b).

**Table 1 Tab1:** Outcomes and instruments

**Outcome**	**Instrument**
Values clarity subscore	Decisional Conflict Scale (DCS) [16]
Self-efficacy	Decision Self-Efficacy Scale (DSES) [18]
Preparation for decision-making	Preparation for Decision Making Scale (PDMS-D) [19]
Patient involvement	Patient Involvement in Care Scale (PICS) [20]
Quality of life	EQ-5D-5L [21]
Anxiety and depression	Hospital Anxiety and Depression Scale (HADS-D) [22, 23]

### Participant timeline {13}

Participation in the study includes the completion of two questionnaires for each participant (before and after the medical consultation at intervals of 1–4 weeks). The questionnaires will be handed over personally (including a stamped return envelope) or sent by e-mail. The time needed to answer the questionnaires is about 10 min.

In addition to the questionnaire survey, the application of the decision aid incl. decision coaching will be carried out with participants in the intervention group. This can take place, depending on the patient’s wishes, either in the clinic or at another location, by telephone or by video conference. The time frame is about 30–45 min for the decision aid and the accompanying conversation. Appointments are made in person, by phone, or by mail.

The total study-related time required is therefore about 20 min for persons who participate exclusively in the questionnaire survey and about 50 to a maximum of 65 min for persons who are invited both to the questionnaire survey and to the decision coaching (Figs. 1 and 2).

**Fig. 1 Fig1:**
[figure not shown]
Schedule of enrolment, interventions, events, and assessments (SPIRIT figure). ** Timepoint: t_3_= consultation with physician (decision making), −t_1_ and t_0_ = 6–8 days before physician consultation, t_1_ and t_2_ = 2–5 days before physician consultation, t_4_ = 1–14 days after physician consultation

**Fig. 2 Fig2:**
[figure not shown]
Participant timeline

### Sample size {14}

A clinically relevant difference of 10 points in the primary outcome between the two treatment groups was assumed to show a sufficient clinical difference for case planning. In addition, the standard deviation was estimated to be 20.6 from the literature [12]. Under these assumptions, *n*=71 patients per group are needed to demonstrate the assumed difference between the two groups at a two-sided significance level of 5% with a power of 80% using a Mann-Whitney *U* test. The calculation was performed by means of 100,000 simulation runs using the case number software PASS v 16.0.4. Taking into account a dropout rate of approx. 20%, 71/(1–0.20)=89 patients per group are included. These results in a total number of cases of *n*=178 patients are to be included in the study.

### Recruitment {15}

Patients are identified by the recruiting research assistants in CT- and indication conferences and tumor board meetings and on oncological wards. If patients meeting the eligibility criteria are identified, recruitment takes place when the patients are in the clinic for their examination appointments like MRT, bronchoscopy, etc. The expected recruitment rate is five to eight patients per week from March 2022 to December 2022.

The research assistants introduce themselves and the study to the patients and, if patients are willing to participate, they get the information sheet and sign the consent form. After that, randomization takes place.

## Assignment of interventions: allocation

### Sequence generation {16a}

Randomization to the two groups of the study (control and intervention group) will be performed in a ratio of 1:1. Stratified block randomization will be performed according to the characteristic of preferred decision-making at baseline (expressions: physician should decide; patient would like to decide alone; patient and physician should decide together). This is to ensure that participants are evenly distributed within the study groups according to their preferred decision style, since it is assumed that the intervention effect differs according to the individual differences in preferences for decision style.

### Concealment mechanism {16b}

Allocation concealment will be ensured by using opaque, sealed envelopes provided by the Institute of Medical Biometry, and takes place after the patients have been recruited.

### Implementation {16c}

After they have given written consent, participants are enrolled on the study. The recruiting research assistant opens the sealed envelopes and assigns patients to the intervention vs. control group according to the preferred decision-making style.

Participants in the control group receive the questionnaires and are instructed to return the filled-in questionnaires before their next consultation with their physician. Participants in the intervention group are informed that the decision coaching will take place before their next consultation and that they will be approached by the decision coach to make the appointment. The questionnaires are given to them after the decision coaching has taken place and before the consultation with the physician.

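### Intervention patients get the primary-outcome questionnaire only after coaching, controls without condition, and no route is stated for measuring the uncoached, so the intention-to-treat estimate leans toward the effect in coached patients

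*Protocol article*

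**What the plan says.** Implementation {16c} sets two different triggers for handing out the questionnaire that carries the primary outcome. For controls: "Participants in the control group receive the questionnaires and are instructed to return the filled-in questionnaires before their next consultation". For the intervention arm: "The questionnaires are given to them after the decision coaching has taken place and before the consultation with the physician". The section on decision coaching gives the same order of events, and the Primary outcome section builds it into the definition of the endpoint, the values-clarity score "in the Decisional Conflict Scale (DCS) after the decision coaching has taken place".

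Non-attendance is foreseen. Strategies to improve adherence {11c} plans a telephone reminder the day before, with the aim of "ensuring that patients show up for the arranged coaching session". No section says how or when an intervention patient who is not coached completes the first questionnaire.

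On the analysis side, {20c} states: "The intention-to-treat population considers all patients as randomized regardless of whether they finished the whole survey procedure". It also states: "Missing values in the primary outcome (and in other outcomes) are replaced by multiple imputation". The imputation uses predictive mean matching, which borrows values from observed patients. Two other places bear on the point. The per-protocol criteria in {20c} require that the patient "answered the first questionnaire before the decision-making (and for IG: after the intervention". Criteria for discontinuing {11b} says that data already collected from dropouts are left out of the analysis.

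**The concern.** Randomisation protects the comparison only if outcomes are sought in the same way in both arms. Here a control patient receives the instrument because of being allocated, while an intervention patient receives it because of having been coached. The second condition is a post-randomisation event with no counterpart in the control arm.

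If the hand-out rule is followed as written, every observed intervention-arm score comes from a coached patient. The intention-to-treat set still contains the uncoached, but their scores must come from a model that has never seen an uncoached intervention patient. The result reported as the effect of offering HELP would then move toward the effect in those who took it up, and it would lean on intervention patients well and willing enough to attend.

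**Working it through.** **Inputs from Sample size {14}:** difference 10 points, SD 20.6, two-sided 5%, power 80%, 71 per group, 20% dropout, 89 per group, 178 in total.

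**Assumptions, because the document gives no figures:** a share m of 5, 10 or 20% of the intervention arm is uncoached; coached patients gain 10 points; uncoached patients gain nothing and otherwise resemble controls; all uncoached intervention scores are missing and no others are.

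**Step 1, the plan's own figure.** Normal approximation: n = 2 × (20.6 × (1.960 + 0.842) / 10)² = 66.6, so 67 per group. Dividing 66.6 by the Mann-Whitney efficiency 3/π = 0.955 gives 69.8, so 70, against the stated 71. Simulated Mann-Whitney power at 71 per group with normal data is 0.806 (20,000 runs). 71 / 0.80 = 88.75, so 89 per group and 178 in total. The sample size reproduces and is not in dispute.

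**Step 2, true intention-to-treat effect.** It equals 10 × (1 − m).

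**Step 3, what the imputation targets.**
- With arm in the imputation model, an uncoached patient receives a value typical of coached patients. The estimate is about 10 and the bias is 10m.
- Without arm, donors come from the pooled observed scores, with (1 − m) coached patients for each control. Their mean benefit is 10(1 − m)/(2 − m), and the bias is m times that. For m = 10%: 9.0/1.9 = 4.74, and 0.10 × 4.74 = 0.47.

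| Uncoached share m | True effect | Estimate, arm in model | Bias (overstatement) | Estimate, arm not in model | Bias |
|---|---|---|---|---|---|
| 5% | 9.5 | 10.0 | 0.5 (5.3%) | 9.74 | 0.24 |
| 10% | 9.0 | 10.0 | 1.0 (11.1%) | 9.47 | 0.47 |
| 20% | 8.0 | 10.0 | 2.0 (25.0%) | 8.89 | 0.89 |

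**Step 4, check by simulation.** Predictive mean matching with 89 per arm, 5 donors, 5 imputations and 600 runs:
- With arm: 9.71 against a true 8.73 at m = 10% (excess 0.98), and 10.14 against 8.17 at m = 20% (excess 1.97).
- Without arm: 9.41 against 8.94 (excess 0.47), and 8.99 against 8.08 (excess 0.91).

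The levels carry simulation noise; the excesses agree with Step 3. These are differences in means, whereas the planned test is the rank-based van Elteren test, so they show direction and rough size.

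**Step 5, power if everyone is measured.** With 89 per arm, the effective n is 89 × 0.955 = 85 and the SE is 20.6 × √(2/85) = 3.16. Power for 9.5, 9.0 and 8.0 points is 0.852, 0.813 and 0.716, against 0.886 for the full 10 points.

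**The case against.** The strongest reply is that {16c} describes the normal sequence and does not say that non-attenders are refused the questionnaire. The per-protocol clause quoted above would be redundant if every intervention-arm questionnaire followed coaching, and the full protocol behind this article may contain a missed-appointment rule. This stands in part. A reader might infer that uncoached patients certainly have no outcome; the text does not go that far. But nothing shown provides a way for an uncoached questionnaire to arise, so the clause is a reason to reconcile {16c} with {20c}.

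A reader might also infer that the uncoached are imputed exactly as if coached. That is close to true only if arm is in the imputation model, which the article does not say. Nor does it follow that the intention-to-treat effect cannot be obtained at all: measuring everyone would give it, and control-based imputation can approach it under a stated assumption. {20c} already names a sensitivity analysis for missing data, and leaving its assumption to the analysis plan is normal.

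The size is assumed. A 20% uncoached share would equal the whole dropout allowance, which covers both arms and all causes. Patients too ill to answer are lost from either arm; only those able to answer but not coached create the asymmetry. Coaching by telephone or video and the reminder call should keep that group small.

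Two larger figures are tempting and should not be used as the size of this defect:
- Power of 72% or 62% (m = 10% or 20%) is correct arithmetic at 71 per arm. But under the fix non-attenders are measured, and the remaining loss is ordinary non-adherence dilution, not a result of questionnaire timing.
- A false-positive rate of about 9% needs 20% selective non-attendance and a 10-point deficit in non-attenders. The document supports neither.

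**Conclusion.** The concern holds as a fault in how outcome collection is fixed. Outcome collection depends on receipt of the intervention in one arm and on nothing in the other, with no stated route for the uncoached. This is trial conduct laid down in the protocol, and no analysis plan can recover scores that were never collected.

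Under the stated assumptions the bias is upward with either imputation model: 0.5 to 2.0 points with arm in it and about 0.2 to 0.9 without, for 5 to 20% uncoached. If nearly all intervention patients are coached, the bias is small. The handling of these patients is also internally inconsistent: {11b} drops the data of dropouts, while {20c} keeps everyone randomised and imputes. Excluding the uncoached would not help, because coached patients would then be compared with all controls and the target would again be 10 points.

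**What to change.** In the decision coaching section and in {16c}, state that every randomised intervention patient is given or mailed the pre-consultation questionnaire in the same pre-consultation window as controls, whether or not coaching took place. Record coaching as yes or no, and analyse all returned questionnaires as randomised. Reconcile {11b}, {16c} and {20c}, so that one rule says whose data are collected, kept and imputed.

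Trial status expected recruitment to end around 31.01.2023, and the article is dated 2023-05-25, so collection may already be over. In that case, report coaching receipt and primary-outcome missingness by arm, and specify a control-based (reference-based) imputation sensitivity analysis for uncoached intervention patients.

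The cost is low. While collection is open, it is a change of hand-out wording, one extra data item and the use of envelopes and reminder calls that already exist; afterwards, it is one table and one sensitivity analysis. The downside is that the estimated effect may be slightly less favourable.
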